### Acupuncture groups

All acupuncture points are punctured by filiform needles. After being needled, the points will be punctured again using auxiliary needles 2 mm lateral to the first needle, and to a depth of 2 mm without manual stimulation. G6805-1A electro-acupuncture apparatus (Shanghai Huayi, made in Jiangsu, China) is used for electric stimulation at every acupuncture point. Each acupuncture needle and auxiliary needle of each point is connected with electricity by G6805-1A for 30 min, using continuous wave. The stimulation frequency is 20 Hz. The stimulation intensity varies from 0.1 mA to 1.0 mA until the patients feel comfortable.

Sterile, disposable Hwato needles are used in this trial, which are made in Suzhou, China; they are 25 to 50 mm in length and 0.3 mm in diameter. The auxiliary needles are of the same brand with 13 mm in length and 0.16 mm in diameter. De qi sensation will be achieved in the acupuncture groups, through lifting and thrusting combined with twirling and rotating the needles. After retaining the needles for 30 min, all needles are taken out with clean cotton balls to avoid bleeding.

Every patient will receive 16 treatments in total over a period of 4 weeks. Five times a week, with once a day for 5 days continuously with a 2-day interval in the first 2 weeks; three times a week, every 2 days with a 1-day interval in the last 2 weeks.

### Control group

Participants will be orally given Mosapride Citrate tablet with a dose of 5 mg, three times a day for 4 weeks continuously.

### Outcome measurement

The primary outcome in this trial is the number of times of defecation throughout the fourth week after randomization. The primary outcome will be measured at the other time points (2 and 8 weeks after randomization) but as a secondary analysis. The second outcomes include the following five items: shape and properties of stool; intensity of defecating difficulty; MOS item Short Form health survey (SF-36); Self-Rating Anxiety Scale (SAS); and Self-rating Depression Scale (SDS). The first two of second outcomes are measured in 1 week before randomization and 2, 4, and 8 weeks after randomization. Other second outcomes are measured 1 week before randomization and 2 and 4 weeks after randomization, but SF-36 is measured before randomization and 4 weeks after randomization.

All patients have to fill in constipation diaries 1 week before randomization (baseline phase) and 2, 4, and 8 weeks after randomization.

All participants will receive routine tests of blood, urine, and stool, and electrocardiogram (ECG), liver function (ALT, AST), kidney function (BUN, Scr) before randomization, in order to exclude patients who have serious heart, liver, and kidney disease, or other severe disease. Only routine tests of stool should be done twice before randomization and after accomplishment of acupuncture treatment.

During the trial, all adverse events, including bleeding, hematoma, fainting, serious pain, local infection, and so on, are to be recorded during treatment and the follow-up period. Serious adverse events should be reported to the principal investigator immediately. All details will be documented and treatment options for rescue should be given at once. To guarantee the quality of the study, all acupuncturists are required to attend special training classes. The purpose of these training classes is for acupuncturists to understand all the details of this trial. The special training classes have theoretical and practical lessons. For instance, they will be trained to use the central randomization method, to fill in the case report form, to find the correct points, to manipulate the needles, to choose electro-acupuncture apparatus, and so on. After attending all training classes and passing the special training test, acupuncturists are qualified to perform this trial. Additionally, to ensure the quality of this trial, the clinical monitors will check the processes of the trial and documenting the details of the processes once a month in every hospital. Moreover, monitors named by the principle investigator will check the accuracy and validity of the original data from the clinical centers.

Patient drop-outs and their reasons, and patients’ compliance will be recorded at the fourth week after randomization.

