**Figure 2 F2:**
[figure not shown]
**Trial processes chart.** SF-36, MOS item Short Form health survey; SAS, Self-Rating Anxiety Scale; SDS, Self-rating Depression Scale.

Participants will receive 16 sessions of acupuncture treatment over 4 weeks, with a treatment frequency of five times a week in the first 2 weeks and three times a week in the last 2 weeks. Each session will last 30 min. The follow-up period lasts 4 weeks (5 to 8 weeks after randomization). Participants will be asked to fill in constipation diaries from 1 week before randomization to 9 weeks after randomization. All outcomes are assessed at baseline and 2, 4, and 8 weeks after randomization according to the diaries.

The total research period within this study is 9 weeks for each patient. All patients are asked to record constipation diaries for 1 week before randomization (baseline phase). If they are eligible for this trial, they will be asked to finish diaries from 0 to 8 weeks after randomization.

This trial protocol has been approved by local institutional review boards and ethics committees (April 2011), and follows the principles of the Declaration of Helsinki (Version Edinburgh 2000). Before randomization all patients will be requested to sign the written informed consent, meanwhile they will be given enough time to decide whether they are willing to participate this trial, or they choose other treatment options.

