### Sample size calculation and statistical analysis

According to the previous literature [16], an improvement of 2.6 times (standard deviation 2.4) for defecating during 1 week with functional constipation by prucalopride is reported, and a difference of 1.6 times between groups is considered to be of clinical relevance [16]. In this study, we anticipated an improvement of 4.0 times by Shu-Mu points group, 3.8 times by He points group, 5.2 times by Shu-Mu-He points group, and 2.6 times by Mosapride Citrate tablet group. A standard deviation of 6.0 is considered, to allow a relatively high heterogeneous variance in this population. Moreover, we mainly focus on the comparison of Shu-Mu-He points group *vs*. Mosapride Citrate tablet group. So the between-group comparison will be done as: first, Shu-Mu-He points group will be compared with Mosapride Citrate tablet group as the primary comparison, since the prescription of Shu-Mu-He points is considered to be better than the other two acupuncture protocols; second, comparisons among acupuncture groups will be performed also as exploratory analysis. So, we used GPower 3.1.3 [Franz Faul, Universität Kiel, Germany], and input the four group mean defecation rates as 4.0, 3.8, 5.2, and 2.6 per week, with a common assumed standard deviation of 6.0, giving a calculated effect size of 0.15. With four groups of equal size (175/group, 700 in total) this gives the study 90% power at a 5% level of significance to detect such an overall effect size using a one-way ANOVA fixed effects omnibus test, and assuming a 15% loss to follow-up. For the pairwise comparison of primary interest (Shu-Mu-He *vs*. mosapride citrate) the study has over 90% power at a 1% level of significance (to make some adjustment for multiple comparisons) to detect a mean difference of 2.6 (5.2 to 2.6) assuming the common standard deviation of 6.0 defecations with 175 participants per group.

Statistical analysis will be performed by the Clinical Evaluation Center of China Academy of Chinese Medical Sciences in Beijing. The statistician is blinded from the allocation of groups. SPSS13.0 and SAS9.0 statistical software packages will be used to analyze the data.

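### The analysis stated for the week-4 defecation count has no baseline covariate, although every patient records a baseline week; adding one is a free gain in precision

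*Protocol article*

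**What the plan says.** **Endpoint.** Under Outcome measurement: "The primary outcome in this trial is the number of times of defecation throughout the fourth week after randomization". The Abstract and the Discussions section also describe a weekly frequency in week 4. None of the three names a change from baseline.

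**Baseline data.** The text after Figure 2 in Methods and design says: "All patients are asked to record constipation diaries for 1 week before randomization (baseline phase". The same section lists baseline among the assessment times for all outcomes.

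**Analysis.** The section Sample size calculation and statistical analysis powers a one-way fixed-effects ANOVA. It then names ANOVA for numerical variables, Kruskal-Wallis for skewed data, and repeated measures analysis across time points. No covariate is mentioned. The one stated use of baseline characteristics is description by group. A detailed statistical analysis protocol is said to have been developed, but it is not shown.

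**Planning values.** The same section starts from a published result, "an improvement of 2.6 times (standard deviation 2.4) for defecating during 1 week", and continues: "we anticipated an improvement of 4.0 times by Shu-Mu points group, 3.8 times by He points group, 5.2 times by Shu-Mu-He points group", with 2.6 for mosapride. A few lines later the authors "input the four group mean defecation rates as 4.0, 3.8, 5.2, and 2.6 per week". One SD, 6.0, is used for all four groups, and the resulting effect size is reported as 0.15. The section does not say whether 6.0 is the SD of the count or of the change.

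**The concern.** The raw week-4 count includes each patient's usual bowel frequency, and the baseline week measures part of that. An analysis that leaves it out keeps this explainable variation in the error term. It also leaves any chance imbalance in baseline frequency in the estimated difference. Both are covered by the standard error, but at the price of a wider interval and less power than the same data could give. The primary comparison is tested at 1%, so precision matters.

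A lesser matter is that the four planning values appear once as improvements and once as weekly rates. The SD of a count and the SD of a change generally differ, so a reader cannot tell which variable the power calculation describes.

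**Working it through.** **Inputs from the article:** planning means 4.0, 3.8, 5.2 and 2.6; SD 6.0; 175 per group (700 in total); 15% loss; 5% level for the omnibus test; 1% level and a difference of 2.6 for Shu-Mu-He versus mosapride. I take the 1% test as two-sided. **Assumption:** the baseline to week-4 correlation r is not in the article, so it is shown over a range.

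**1. Reproduce the omnibus power.** The grand mean is 3.9 and the squared deviations are 0.01, 0.01, 1.69 and 1.69, with mean 0.85. So f = √0.85 / 6.0 = 0.154 (stated as 0.15). With noncentrality N·f² and the noncentral F distribution on 3 and N − 4 degrees of freedom:
- N = 700: power 94.0%
- N = 700 × 0.85 = 595: power 89.5%

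The stated 90% after loss is reproduced.

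**2. Reproduce the pairwise power.** The noncentrality is 2.6 / (6.0·√(2/n)), used with the noncentral t distribution on 2n − 2 degrees of freedom.
- n = 175: SE 0.641, noncentrality 4.05, critical value 2.59, power 92.8%. The stated figure of over 90% is reproduced.
- n = 175 × 0.85 = 148.75: SE 0.696, noncentrality 3.74, power 87.3%.

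**3. Add the baseline covariate, taking 6.0 as the raw-count SD.** The residual SD is 6.0·√(1 − r²), so the variance falls by r². The one degree of freedom spent on the covariate is ignored.

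| r (assumed) | Residual SD | Variance removed | Power, 175 per group | Power, about 149 per group |
|---|---|---|---|---|
| 0 (no adjustment) | 6.00 | 0% | 92.8% | 87.3% |
| 0.3 | 5.72 | 9% | 95.1% | 90.7% |
| 0.5 | 5.20 | 25% | 98.1% | 95.7% |
| 0.6 | 4.80 | 36% | 99.3% | 98.1% |

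The fall from 92.8% to 87.3% in the first row comes from the 15% loss and has nothing to do with adjustment. The effect of adjustment is read down each column.

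**4. What the unclear scale changes.** Randomization gives the groups the same expected baseline, so the expected group difference is 2.6 on either scale. Only the SD is in question. If 6.0 were the SD of the change, and baseline and week-4 variances were equal, the raw-count SD would be 6.0 / √(2(1 − r)). By the method of step 2, with about 149 per group:

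| r (assumed) | Raw-count SD | Power, unadjusted | Power, ANCOVA |
|---|---|---|---|
| 0.3 | 5.07 | 96.6% | 97.9% |
| 0.5 | 6.00 | 87.3% | 95.7% |
| 0.7 | 7.75 | 61.9% | 92.7% |

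Under this reading the unadjusted count does better than planned when r is below 0.5 and worse when r is above 0.5.

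**The case against.** The strongest reply is that nothing in the plan is wrong. Unadjusted ANOVA in a randomized trial is unbiased and controls the type I error, chance baseline imbalance is already allowed for in its standard error, and both stated power figures reproduce. At r = 0.3 and 175 per group, adjustment adds only about 2 percentage points, and if r is near zero it adds nothing. Covariates are also often settled in a separate analysis document, and one is said to exist. All of this stands, and it limits the point to an improvement of a stated method.

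Four stronger readings are tempting, and the article does not support them:

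- **The baseline count is unused.** It is described by group, it may enter the repeated measures analysis, and the analysis protocol that is not shown could adjust for it. All that can be said is that no inferential use is stated.
- **The SD was taken over from improvement data.** The cited improvement SD is 2.4. The plan uses 6.0 and explains it as an allowance for a heterogeneous population.
- **The scale could be chosen after seeing the data.** The Abstract, Outcome measurement and Discussions all fix the week-4 count. The loose labelling is confined to the planning values.
- **The trial has less power than it claims because baseline is omitted.** Power is lower only relative to ANCOVA. If 6.0 is the raw-count SD, the stated figures stand.

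**Conclusion.** The point holds as a free improvement. The article names an unadjusted analysis for an outcome whose baseline value is recorded for every patient. For any nonzero correlation, ANCOVA estimates the same difference more precisely. With 6.0 as the raw-count SD and r from 0.3 to 0.6, it removes 9% to 36% of the variance. That adds about 2 to 7 percentage points of power to the primary comparison at 175 per group, and about 3 to 11 points at about 149 per group. The direction of the gain is certain for nonzero r, but its size is not, because r is not given.

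The change of label from improvement to weekly rate is a real inconsistency but a secondary one. It does not alter the expected group difference, and it matters only for what the SD of 6.0 means.

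**What to change.** 1. Keep the week-4 count as the single primary endpoint.
2. State that it will be analysed by ANCOVA with the baseline-week count as covariate, or by a mixed model over weeks 2, 4 and 8 with the same covariate. Report the adjusted mean difference between Shu-Mu-He and mosapride with its confidence interval.
3. In the sample-size section, say whether 4.0, 3.8, 5.2, 2.6 and the SD of 6.0 refer to the count or to the change from baseline, and add that the expected group difference is the same on both scales.

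The cost is a few sentences in the analysis text. No new data are needed because the baseline diary is already part of the trial. The article reports 340 of 700 participants recruited, so the model can be fixed before the outcome data are analysed. If the analysis protocol that is not shown already names this covariate, it is enough to say so.

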### Sample size calculation and statistical analysis

According to the previous literature [16], an improvement of 2.6 times (standard deviation 2.4) for defecating during 1 week with functional constipation by prucalopride is reported, and a difference of 1.6 times between groups is considered to be of clinical relevance [16]. In this study, we anticipated an improvement of 4.0 times by Shu-Mu points group, 3.8 times by He points group, 5.2 times by Shu-Mu-He points group, and 2.6 times by Mosapride Citrate tablet group. A standard deviation of 6.0 is considered, to allow a relatively high heterogeneous variance in this population. Moreover, we mainly focus on the comparison of Shu-Mu-He points group *vs*. Mosapride Citrate tablet group. So the between-group comparison will be done as: first, Shu-Mu-He points group will be compared with Mosapride Citrate tablet group as the primary comparison, since the prescription of Shu-Mu-He points is considered to be better than the other two acupuncture protocols; second, comparisons among acupuncture groups will be performed also as exploratory analysis. So, we used GPower 3.1.3 [Franz Faul, Universität Kiel, Germany], and input the four group mean defecation rates as 4.0, 3.8, 5.2, and 2.6 per week, with a common assumed standard deviation of 6.0, giving a calculated effect size of 0.15. With four groups of equal size (175/group, 700 in total) this gives the study 90% power at a 5% level of significance to detect such an overall effect size using a one-way ANOVA fixed effects omnibus test, and assuming a 15% loss to follow-up. For the pairwise comparison of primary interest (Shu-Mu-He *vs*. mosapride citrate) the study has over 90% power at a 1% level of significance (to make some adjustment for multiple comparisons) to detect a mean difference of 2.6 (5.2 to 2.6) assuming the common standard deviation of 6.0 defecations with 175 participants per group.

Statistical analysis will be performed by the Clinical Evaluation Center of China Academy of Chinese Medical Sciences in Beijing. The statistician is blinded from the allocation of groups. SPSS13.0 and SAS9.0 statistical software packages will be used to analyze the data.

Prior to all analyses, a detailed statistical analysis protocol was developed. The intention-to-treat (ITT) population was defined as the patients who are randomized and received at least one treatment session. The per-protocol (PP) population was defined as the patients who completed the study and do not have major protocol violations. All analyses were based on the ITT population and PP population. And the result of the ITT analysis will be compared with that of the PP analysis to check whether the results are consistent.

First of all, baseline characteristics will be analyzed by descriptive statistics for each group. Then analysis is done to make comparisons among the treatment groups and control group. If a significant difference is found by comparison of the treatment groups and the control group, the next step is to make comparisons among three acupuncture points treatment groups in effectiveness. Multiple comparisons will be adjusted according to Bonferroni correction method.

The repeated measures analysis will be used in the different time points assessment. The Kruskal-Wallis test will be employed in the analysis of skewed distribution data. Analysis of variance (ANOVA) is used for numerical variables, and Chi-square test for categorical variables.

There is one acupuncturist in each center to do all three interventions, which probably introduces clustering effect in this trial. Therefore, we calculated the intracluster correlation coefficient from the results of this trial and report the coefficient [17].

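### The power given for the primary pairwise comparison counts all 175 randomised per group; with the 15% loss the same paragraph assumes, it is about 87% at a two-sided 1% level, not over 90%

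*Protocol article*

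**What the plan says.** The sample size section of the protocol article (Sample size calculation and statistical analysis) makes two power statements, one directly after the other.

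- **Omnibus test.** "With four groups of equal size (175/group, 700 in total"), the trial is said to have 90% power at a 5% level "using a one-way ANOVA fixed effects omnibus test, and assuming a 15% loss to follow-up".
- **Primary pairwise comparison (Shu-Mu-He versus mosapride).** Here the article claims that "the study has over 90% power at a 1% level of significance (to make some adjustment for multiple comparisons"). The effect entered is the anticipated gap of 2.6 defecations per week between these two arms, and the calculation is made "assuming the common standard deviation of 6.0 defecations with 175 participants per group".

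The Design section gives 700 as the number to be enrolled and randomised 1:1:1:1. The 175 in both statements is therefore the number randomised to each arm.

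**The concern.** The two statements use the same 175 but treat it differently. The first takes it as the number before loss. The second puts it into the power calculation as if every randomised participant supplied the week-4 outcome. The second sentence applies no loss and does not say that attrition is irrelevant to this comparison.

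This is the comparison the plan calls primary, and the Discussions section presents the sample size as a safeguard of power. If the figure does not survive the plan's own attrition assumption, readers are told that the chance of missing the anticipated effect is below 10% when, on the plan's own inputs, it is higher.

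**Working it through.** **Inputs**, all from the sample size section: difference d = 5.2 − 2.6 = 2.6; SD = 6.0 in each group; level 1%; 175 per group; 15% loss. Sidedness is not stated for this comparison and is taken as two-sided.

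**Step 1: reproduce the stated figure (no loss).** Normal approximation: power = Φ(d / (SD·√(2/n)) − z), with z = 2.576 for two-sided 1%.
- n = 175: SD·√(2/n) = 6.0 × 0.1069 = 0.641; 2.6 / 0.641 = 4.05; Φ(4.05 − 2.576) = 93.0%.
- The two-sample noncentral t gives 92.8%, and 92.9% with the error degrees of freedom pooled over four groups.

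So the claim of over 90% is right if all 175 per group are analysed.

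**Step 2: confirm that 175 is the number before loss.** The four means 4.0, 3.8, 5.2 and 2.6 average 3.9. The squared deviations are 0.01, 0.01, 1.69 and 1.69, with mean 0.85 and root 0.922. Hence f = 0.922 / 6.0 = 0.1537, printed as 0.15.
- Omnibus power at 5% with all 700 analysed: 94.0%.
- Omnibus power with 149 per group (4 × 149 = 596): 89.6%, which rounds to the stated 90%.

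The stated 90% fits 175 as the number before loss and does not fit 175 as the number analysed.

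**Step 3: apply the loss to the primary comparison.** 175 × 0.85 = 148.75, so 148 to 149 evaluable per group.
- n = 149, normal: 6.0 × √(2/149) = 6.0 × 0.1159 = 0.695; 2.6 / 0.695 = 3.74; Φ(3.74 − 2.576) = 87.8%.

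| Evaluable per group | Two-sample t | t, pooled df | Normal |
|---|---|---|---|
| 175 | 92.8% | 92.9% | 93.0% |
| 149 | 87.4% | 87.6% | 87.8% |
| 148 | 87.1% | 87.3% | 87.5% |

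By the two-sample t, the type II error goes from 100 − 92.8 = 7.2% to 100 − 87.4 = 12.6%.

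**Step 4: number needed.** For 90% power at two-sided 1%, 161 evaluable per group are needed by the t-test (159 by the normal approximation). With 175 randomised, that allows a loss of (175 − 161) / 175 = 8%, about half of what the plan assumes.

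**Step 5: sensitivity to the level** (149 per group, two-sample t). Two-sided 5%: 96%. One-sided 1%: 91.9%.

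**The case against.** **The sentence states its own condition.** It says "with 175 participants per group", and on that condition it is correct. This stands: the formula was applied correctly, and the fault is an attrition basis that changes between adjacent sentences. It does not rescue the claim, because the plan itself expects fewer than 175 to be evaluable.

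**The shortfall depends on a two-sided 1% test.** At two-sided 5%, or one-sided 1%, power stays above 90% after loss. It also does at two-sided 1.67%, where a Bonferroni split over three comparisons with mosapride (an assumption) gives 90.8%; a split over all six pairs (0.83%) gives 86.0%. This is fair and limits the point to the level the article chose. But 1% is the level attached to the claim, and no one-sided test is stated. The rationale section mentions non-inferiority, but the sample size section gives no margin and powers for detecting a difference.

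**The intention-to-treat population keeps dropouts.** It is defined as those randomised who received at least one session. The primary outcome, however, is a week-4 diary count, which participants lost earlier do not supply. The plan's own omnibus calculation also counts loss against the sample size.

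**The SD is cautious.** The article cites 2.4 and uses 6.0; at an SD of 5.7 and 149 per group the power is already 91.0%. This bears on how much the gap matters, not on whether the statement agrees with its stated SD.

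**Stronger readings that the document does not support.** A reader might infer that the omnibus power is also wrong. With the exact inputs it is 89.6%. The lower figure of 87.9% comes only from feeding the rounded f of 0.15 back in, whereas the article says the means and SD were entered. A reader might also note that "a difference of 1.6 times between groups is considered to be of clinical relevance" while power is reported only for 2.6, and count this as part of the error. Powering on an anticipated effect larger than the smallest relevant one is a separate design choice and has no bearing on the 175 versus 149 discrepancy.

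**Conclusion.** Wrong as written; should be fixed. Under the plan's own 15% loss, the primary comparison has about 87% power at a two-sided 1% level (87.1% to 87.8% by formula and rounding), not over 90%. The gap is 2 to 3 points below the stated threshold and about 5 points below the no-loss figure.

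This rests on a two-sided test, loss spread evenly over the arms, and lost participants contributing no week-4 outcome. It does not show that the trial is too small or that the design must change. The error lies in one printed figure, and at two-sided 5% the power after loss is still about 96%.

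**What to change.** Restate the pairwise power on the same basis as the omnibus test and name the sidedness. Suggested wording: *Allowing for 15% loss to follow-up (about 149 evaluable per group), the comparison of Shu-Mu-He with mosapride has about 87% power at a two-sided 1% level (96% at 5%) for a mean difference of 2.6 with a standard deviation of 6.0.* The omnibus sentence can stay as it is.

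The cost is one reworded sentence and a slightly less favourable figure. Enrolment, tests and analysis populations are unchanged, so the correction can be made with recruitment already under way (340 enrolled, according to the Trial status section).

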## Methods and design

### Design

This is a randomized controlled, four-arm, large-scale trial comparing three acupuncture groups (using different acupuncture points) with Mosapride Citrate control group (Figures 1 and 2). Seven hundred participants will be included from the following eight hospitals: Guang’anMen Hospital of China Academy of Chinese Medical Sciences; First Affiliated Hospital of Chengdu University of Traditional Chinese Medicine (TCM); Affiliated Hospital of Anhui College of TCM; Affiliated Hospital of Changchun University of TCM; Affiliated Hospital of Guangzhou University of TCM; Affiliated Hospital of Hunan University of TCM; Affiliated Hospital of Shandong University of TCM; and Affiliated Hospital of Shanxi College of TCM. These participants will be randomly assigned to four groups (three acupuncture groups and Mosapride Citrate control group) through central randomization in a 1:1:1:1 ratio. The central randomization system will be used and performed by the Clinical Evaluation Center at the China Academy of Chinese Medical Sciences in Beijing. A random number and group assignment will be immediately received by telephone, mobile phone, or website sent from the Clinical Evaluation Center.

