#### Recruitment procedures

Two strategies will be used to recruit participants with functional constipation. The first is to recruit participants in outpatient clinics from the eight hospitals. The chief physicians of gastroenterology and colorectal department in each hospital were invited to attend a discussion of how to recruit patients. Research assistants will be sent to their departments to help screen participants. Moreover, posters of this trial were shown outside the clinics to attract possible candidates. Second, we will post advertisements through TV broadcasts, newspapers, and so on. In these advertisements, we will briefly introduce the population we want to include, and mention the free acupuncture treatments for participants who are eligible.

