According to recommendations of a responder in clinical trials for functional gastrointestinal disorders [24], self-reported diaries will be used in this trial. The participants will know whether they receive acupuncture or medication, but will not know which type of acupuncture they have received, therefore, participants in Mosapride group might bias the outcome assessment. The primary outcome and the secondary outcomes will be calculated from the diaries. Considering that the frequency of defecation is the most important concern of patients with functional constipation, and that acupuncture may be of best effect at the end of the treatment [25,26], we choose the number of times for defecating during 1 week in the fourth week after randomization [24].

Due to lack of clear evidence of effectiveness with acupuncture to treating functional constipation, our trial aims to clarify this issue by means of a multicenter randomized controlled large-scale trial.

In conclusion, the results of this trial are expected to confirm whether acupuncture is effective in the management of functional constipation and whether traditional acupuncture theories play an important role in it.

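### The population labelled ITT leaves out randomised patients who never start treatment, and no described analysis includes everyone randomised, although the arm is known before treatment starts

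*Protocol article*

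**What the plan says.** All of the following is from the protocol article.

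- **Sample size calculation and statistical analysis** gives the definition: "The intention-to-treat (ITT) population was defined as the patients who are randomized and received at least one treatment session". The second set is narrower: "The per-protocol (PP) population was defined as the patients who completed the study and do not have major protocol violations". The section then says "All analyses were based on the ITT population and PP population" and that the two results will be compared for consistency. The same section makes Shu-Mu-He against mosapride the primary comparison.
- **Design**, on when the assignment is known: "A random number and group assignment will be immediately received by telephone, mobile phone, or website sent from the Clinical Evaluation Center".
- **Discussions**, on blinding: "The participants will know whether they receive acupuncture or medication, but will not know which type of acupuncture they have received".
- **Recruitment procedures**: outpatient clinics are the first route. Advertisements are the second, and they "mention the free acupuncture treatments for participants who are eligible".
- **Control group**: "Participants will be orally given Mosapride Citrate tablet with a dose of 5 mg, three times a day for 4 weeks continuously".

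**The concern.** An ITT analysis keeps every randomised patient in the assigned group, so that the groups differ only by chance at the start. The article's definition adds a condition that is met, or not, after randomisation. That does little harm when the decision to start cannot depend on the assigned arm. Here it can: the assignment is released first, and acupuncture against tablets is unblinded. The primary comparison lies across that unblinded boundary. Among the three acupuncture arms the risk is weaker, because patients are masked to the type of acupuncture.

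Two features make it worse. The planned check compares ITT with per-protocol, but a patient who never started is in neither set. And the entry condition is worded in sessions, while the control arm takes tablets three times a day; the article does not say what counts as having been treated on mosapride.

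This is a rule that the article states, not a detail that an article would leave to the analysis plan.

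**Working it through.** **1. Inputs from the article** (Sample size calculation and statistical analysis): 175 per group; anticipated difference 5.2 - 2.6 = 2.6 per week; planning SD 6.0; SD reported in the cited prucalopride literature 2.4; clinically relevant difference 1.6 per week; 1% level for the primary pairwise comparison. Sidedness is not stated; two-sided is assumed.

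**2. The plan's own figure.** The article claims over 90% power for the pairwise comparison.
- SE = 6.0 × √(2/175) = 0.641
- 2.6 / 0.641 = 4.053; 4.053 - 2.576 = 1.478; Φ(1.478) = 0.930

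The claim reproduces. The calculation counts all 175 randomised patients per group, so analysing everyone randomised changes no stated figure.

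**3. Who is in each set**

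| Patient | ITT as defined | Per-protocol | All randomised |
|---|---|---|---|
| Completes without major violation | in | in | in |
| Starts, then stops or violates | in | out | in |
| Randomised, never starts | out | out | in |

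The two planned sets differ only in the second row. Their agreement says nothing about the third.

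**4. Size, under assumptions.** Let q be the share of the mosapride arm that never starts, and D the difference between the mean that those patients would have had and the mean of those retained. Then

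shift in control mean = q × D.

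Assumed, since the article gives no rates: non-start in the mosapride arm only, q of 2%, 5% or 10%, and D = 0.5 SD. That makes D = 0.5 × 2.4 = 1.2 or 0.5 × 6.0 = 3.0 per week.

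| q | Shift at SD 2.4 | % of 1.6 | Shift at SD 6.0 | % of 1.6 |
|---|---|---|---|---|
| 2% | 0.024 | 1.5 | 0.06 | 3.8 |
| 5% | 0.06 | 3.8 | 0.15 | 9.4 |
| 10% | 0.12 | 7.5 | 0.30 | 18.8 |

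**5. Effect on the test.** The SE with exclusions is SD × √(1/175 + 1/(175(1 - q))). Because D is set in SD units, shift/SE is the same at either SD: 0.09, 0.23 and 0.46 for q = 2%, 5% and 10%. With no true difference, the two-sided 1% test then rejects 1.03%, 1.2% and 1.8% of the time.

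An extreme case for scale: q = 15% and D = 6.0 (one SD at 6.0) gives a shift of 0.15 × 6.0 = 0.90 per week and a rejection rate of 10.9%.

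**6. Power.** With 15% of the control arm excluded (175 × 0.85 = 148.75), SE = 0.669, and power for a difference of 2.6 at SD 6.0 falls from 93.0% to 90.5%. The issue is bias, not power.

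**The case against.** The case for leaving this alone has weight, and several parts of it stand.

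- **The mechanism is a possibility, not a shown fact.** A reader might infer that free-acupuncture advertising must drive mosapride patients away. The article does not support that. Clinics are the first recruitment route, and patients consent and keep a one-week baseline diary before randomisation, which filters out the uncommitted. Acupuncture patients face 16 needling sessions in 4 weeks, a reason of their own not to start. The direction is open.
- **The size is assumed.** SD 6.0 was chosen to allow for heterogeneity; at 2.4 the shift per week is 40% as large. Even 10% non-start in one arm gives less than half a standard error.
- **Non-starters need not come on top of the 15% loss to follow-up.** They may already be counted in it.
- **Which population is primary** is not a finding here. The article refers to a detailed analysis protocol that is not shown, and that choice can sit there.
- **Session has a natural reading for tablets**, at least one dose. That makes the wording repairable; the article still does not say it.
- **An all-randomised analysis needs week-4 diaries** that patients who leave at assignment may never supply, so it partly replaces exclusion with imputation.

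None of this removes the core. The stated definition conditions on an event after randomisation, in an unblinded comparison, and neither the blinded statistician nor the ITT/per-protocol comparison guards against it: the exclusion arises from patient behaviour before analysis.

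**Conclusion.** The point holds as a mislabelled population that opens a route to bias in the primary comparison. It does not establish that the randomised comparison is already broken, or that the result will favour acupuncture: the article gives no non-start counts by arm and no outcomes for non-starters.

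Under the stated assumptions (5-10% non-start, mosapride arm only, 0.5 SD difference), the shift lies between 0.06 and 0.30 per week across the two SDs, about 4-19% of the relevant difference of 1.6. It matters little at about 2% or less, and it grows if non-starters are many and very different. Non-start of the same kind in the acupuncture arm would offset part of it. The correction is worth making because it is inexpensive and because reporting never-treated patients by arm would replace these assumptions with data.

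**What to change.** 1. Define ITT as all randomised patients, analysed in the assigned group whether or not treatment started, and use it for the superiority comparison of Shu-Mu-He with mosapride.
2. Keep seeking diaries from patients who do not start. Handle absent diaries with a stated missing-data method and a sensitivity analysis around its assumptions.
3. Relabel the present set as modified ITT, entered by at least one session or one dose, and keep it as a sensitivity set.
4. Report the number of never-treated patients by arm.
5. Per-protocol can stay beside ITT for any non-inferiority comparison, since the rationale for the acupuncture protocol hypothesises that all acupuncture groups are non-inferior to mosapride.

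Cost: a changed definition, a label, and a few more patients to follow up or impute. The sample size does not change. The article reports 340 participants recruited at submission; diaries from any non-starters among them may not be recoverable, and for those patients the analysis would rest on the missing-data method.
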